## 9.2 Sample Size Determination

In a study examining the responsiveness of PROMIS pain impact to changes in chronic pain patients who stated pain was a “little better” had an average increase of 1.8 point with a SD of 6.6 points and “much better” was associated with an average increase of 6.8 points with a SD of 6.5 points.^65^  Based on this we have chosen a change of 5 points as representing a clinically meaningful improvement in chronic pain, with an estimated a SD of 6.5 points. With a sample size of 28 patients (56 total) in each group we will have 80% power to detect a difference of 5 points in change between two groups in pain impact score from baseline at a two-sided 0.05 significance level.

We have a strong track record of following subjects with chronic pain, opioid use, and SCD in ourprior SCD studies have achieved 85-100% retention at 6 months. In our pilot trial we approached 27 patients to enroll 6 on study, we therefore estimate if we approach 280 patients, we can enroll 70. We conservatively estimate a 20% attrition rate, so we will aim to approach 280 patients to enroll 70 to ensure 56 participants completing the study.

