## 5.5 Strategies for Recruitment and Retention

**Recruitment strategy.** Recruitment will be active and passive. Active recruitment will focus on contacting potentially eligible adults with SCD who are treated at Mt. Sinai’s outpatient and inpatient practices and inviting them to participate. We will employ the following recruitment strategies:

1. Referrals from providers. Patients who are seen for in-person or telemedicine visits with providers in the Sickle Cell Program and are potentially eligible will be referred to study coordinators.
2. Advertising in clinical area. Flyers and brochures about the study will be posted in facilities where adults with SCD are treated
3. Community outreach. We will engage community-based organizations and community leaders to optimize community outreach including events such as health fairs and Sickle Cell Awareness Day events and via advertising the study over email and social media. This will be facilitated through existing partnerships with the Sickle Cell Thalassemia Patients Network and the New York chapter of the Sickle Cell Association of America.

**Feasibility of recruitment.** Recruitment will be feasible. We will primarily recruit patients treated for SCD at the Mount Sinai Adult Sickle Cell Center. Approximately 40 unique patients are seen in clinic each month.  Of approximately 450 adults with SCD treated at the Center we estimate half (225) will have chronic pain, of those 25% will be frequent cannabis users and this ineligible for our study (approximately 56) so we estimate we will have approximately 169 eligible patients. However, we have also created a plan for regularly monitoring recruitment and implementing a contingency plan of expanding to additional NYC Sickle Cell programs if needed.

**Recruitment timeline.** We will recruit for 36 months (see Project Timeline), enrolling 2-3 subjects per month. Recruitment will be feasible; based on the numbers above and prior studies, we expect to identify 30-45 potentially eligible individuals per month, screen 33% of those (10-15), and enroll 20% of these screened (2-3 per month). To monitor progress towards prespecified recruitment benchmarks will be examined at each quarter (3m period).

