## 9.4 Statistical Analyses

### 9.4.1 General Approach

We will first conduct descriptive and graphical analyses to check for outlier and abnormal values, verify that distribution of measures meets assumptions of planned statistical tests, and explore the success of randomization. Primary analyses for all aims will be intent-to-treat analyses of data from baseline to week 8, based on group allocation. Secondary analysis will be done removing patients who do not complete at least 4 weeks on study as well as any patients whose urine samples show presence of cannabinoid metabolites other than THC or whose pill counts reveal they took less than 50% of the reported optimized dose.

Statistical analysis will be done assuming all data is non-normal. Continuous data will be described as means and quartiles, categorical data will be described as percentages.  All inferential tests will be two-tailed.

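### Section 9.2 bases 80% power on an SD from a single response category, with almost no margin, and the 280-to-70 accrual step does not follow from the pilot yield

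*Protocol*

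**What the plan says.** Protocol section 9.2 cites a responsiveness study in chronic pain. It reports the change in PROMIS pain impact separately by patients' own rating: a mean of 1.8 (SD 6.6) among those a little better, while the much-better rating "was associated with an average increase of 6.8 points with a SD of 6.5 points". From this the protocol takes both the target difference and the SD: 5 points is chosen to represent "a clinically meaningful improvement in chronic pain, with an estimated a SD of 6.5 points". It concludes that with 28 per group (56 in total) "we will have 80% power to detect a difference of 5 points in change between two groups" "from baseline at a two-sided 0.05 significance level".

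The same section then turns to accrual. The pilot approached 27 patients to enrol 6, and "we therefore estimate if we approach 280 patients, we can enroll 70". With 20% attrition, 70 enrolled is to yield 56 completers.

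On analysis, section 9.4.1 states "Statistical analysis will be done assuming all data is non-normal", and section 9.4.2 names a rank-sum test on change from baseline as the primary comparison.

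**The concern.** There are two independent weaknesses in one short section.

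First, 6.5 describes patients who share one outcome rating. In a randomised arm some participants will be much better, some a little better, some unchanged and some worse. The SD of change across such an arm contains the within-rating spread and also the spread between the rating means. The protocol gives no SD of change for an unselected sample, and of the two SDs it quotes it uses the smaller. If the real SD is larger, the trial has less than 80% power for 5 points, and a null result would be read against a power it does not have.

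Second, the accrual sentence is presented as a deduction from the pilot, but the pilot proportion does not produce the number given. Anyone planning effort from the figure of 280 would expect more participants than the pilot supports.

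**Working it through.** **Inputs.** From section 9.2: difference 5, SD 6.5, 28 per arm, two-sided 0.05, attrition 20%, pilot 6 of 27, category means and SDs 1.8 (6.6) and 6.8 (6.5). From section 6.3: allocation 1:1. From section 9.4.2: rank-sum test.

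**Reproducing the plan.** For a two-sample t-test with standardised difference 5/6.5 = 0.769, 80% power needs 27.5 per arm, rounded up to 28. Power at 28 per arm is 80.7%. Enrolment is 56/0.8 = 70. Both stated figures reproduce.

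**SD across mixed ratings.** If a share p of an arm is much better and 1 − p a little better:

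variance = p × 6.5² + (1 − p) × 6.6² + p(1 − p) × (6.8 − 1.8)²

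- p = 0.50: 21.125 + 21.78 + 6.25 = 49.16, SD 7.01
- p = 0.25: SD 6.92
- p = 0.75: SD 6.87

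The category values come from the protocol; the mixing shares are assumptions. Adding unchanged or worse patients would widen the spread further. The protocol gives no figures for them, so SD 7.5 below is purely an assumed value.

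**Power at 28 per arm for 5 points.** The t-test column uses the noncentral t distribution. The rank-sum column is from simulation with normal data; the large-sample approximation (effective sample size multiplied by 3/π) runs up to about one percentage point higher.

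| SD | Source | t-test | rank-sum |
|---|---|---|---|
| 6.5 | much-better category | 80.7% | about 78% |
| 6.6 | little-better category | 79.5% | not simulated (approximation 77.6%) |
| 7.0 | equal mix of the two | 75% | about 72% |
| 7.5 | assumed | 69% | about 66% |

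The t-test falls below 80% once the SD exceeds about 6.56.

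**Difference detectable with 80% power, 28 per arm.**

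- SD 7.0: 5.3 points (t-test), 5.5 (rank-sum)
- SD 7.5: 5.7 points (t-test), 5.9 (rank-sum)

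**Accrual.**

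- Pilot yield: 6/27 = 22.2%.
- 280 × 6/27 = 62.2, so 62 enrolled.
- 62.2 × 0.8 = 49.8, so about 50 completers or 25 per arm; t-test power at SD 6.5 is then 76%.
- To enrol 70 at that yield: 70 × 27/6 = 315 approached.
- The stated ratio is 70/280 = 25%, which is not 6/27.

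**The case against.** The strongest reply is that the power statement contains no calculation error. That is correct: 80.7% and 70 × 0.8 = 56 both check. The SD point challenges an assumption, and its size cannot be fixed from the protocol. Nor is 6.5 a strict lower limit. Total variance exceeds the average within-category variance inside the source study, but this trial enrols a different population, selected on pain impact and near-daily pain with stable therapy. What stands is the likely direction and the lack of margin.

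The rank-sum penalty is small by itself, two to three percentage points under normality, and for some non-normal shapes that test is the stronger one. It matters only because it adds to the SD problem.

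On accrual, a 25% yield may have a basis. Section 2.2 reports 24 interested patients out of 27, and also three daily cannabis users withdrawn before randomisation, a group this trial excludes. Either route gives 6/24 = 25%. The protocol states neither, so the sentence still does not follow as written, but explaining the 25% would repair it as well as changing the number would.

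Two stronger readings are tempting and are not supported.

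- *The 56 completers are overstated.* They follow from the target of 70 enrolled. Nothing makes 280 a cap. Section 5.5 separately forecasts 2 to 3 per month for 36 months (72 to 108) and provides for other centres if enrolment falls below 75% of target in two subsequent quarters. The 50 completers and 76% power arise only if approaching stops at 280.
- *The centre cannot supply the trial.* Section 5.5 says "so we estimate we will have approximately 169 eligible patients", and one might apply 6/27 to that pool. But the 169 remain after frequent cannabis users have been removed, whereas the pilot's 27 included daily users who were later lost. The product would count that loss twice. Nor does 169 compare directly with 280 people approached, since it is an already filtered pool from about 450 adults.

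**Conclusion.** The point holds in limited form. The 80% is correctly computed from its inputs, but the SD is a within-category figure, likely too small for a randomised arm and with almost no room for error. For 5 points at 28 per arm, a defensible statement is about 75% (t-test) or 72% (rank-sum) at SD 7.0, and 69% or 66% at SD 7.5. SD 7.0 rests on an equal mix of the two quoted categories, and SD 7.5 is assumed; the rank-sum values assume normal data. The true loss is unknown because no whole-arm SD is given.

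Independently, the step from the pilot to 280 approached is wrong as written: it gives 62 enrolled, or needs 315 approached for 70. This affects power only if enrolment actually falls short of 70.

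**What to change.** Revise the text of section 9.2 without adding patients:

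1. Justify an SD of change that applies to all participants in an arm. Failing that, restate the power as a range for the planned rank-sum test: with 56 completers, 80% power for about 5.5 to 5.9 points at SD 7.0 to 7.5 (5.3 to 5.7 by t-test), or roughly 65 to 75% power for 5 points across the two tests. Label the SD values as assumptions.
2. Change 280 to 315 in both places where it appears, or keep 280 and state the basis for a 25% yield.
3. Leave the enrolment target of 70, the recruitment benchmarks and the contingency trigger in section 5.5 unchanged. Lowering them would delay expansion to other centres while the trial was still short of its target.

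The cost is confined to wording: the stated power and recruitment figures become less favourable. Sample size, procedures and analysis do not change.

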## 9.3 Populations for Analyses

Primary analysis of all endpoints will be an intention to treat analysis.  Secondary analysis will be done removing patients who do not complete at least 4 weeks on study as well as any patients whose urine samples show presence of cannabinoid metabolites other than THC or whose pill counts reveal they took less than 50% of the reported optimized dose.   Safety analysis will be done on all patients who took at least one dose of the study medication.

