**Study Intervention Compliance**

**Measures of Adherence:** Blood toxicology and pill count results will be used to determine study drug adherence (both) and adherence to avoidance of other cannabinoid containing substances (blood only) and will be used during secondary non-intention to treat analysis of the data as described below.

**Pill Counts:**Patients should bring medication bottles to visits at weeks 2, 4 and 8.  Pills counts will be done at each visit and compared to pharmacy dispensing records.

**Blood measure of non-dronabinol cannabinoid use:**  Blood cannabinoids test will be done for multiple cannabinoids including THC, cannabidiol (CBD), and others.  This can distinguish 3 states: (1) recent dronabinol alone in which only THC will be present, (2) recent cannabis use, without or with dronabinol, in which multiple cannabinoids will be present and (3) no recent cannabis use in which no cannabinoids will be present.  This was shown to be able to distinguish dronabinol use from other illicit and medical cannabis use in our prior feasibility study.^69^  Blood will be collected at 4 weeks, and 8 weeks on study.

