# 8 Study Assessments and Procedures

## 8.1 Efficacy Assessments

Informed consent will be obtained prior to screening activities. Screening may take multiple visits but must be completed within 30 days of obtaining informed consent. The following assessments will be completed:

- Written Informed consent
- Demographics
- Medical history - Including SCD type, SCD related problems, other medical problems, psychiatric and substance use history, description of pain and pain treatment
- Weight
- Vital Signs
- Review of current and past medications
- Pregnancy test - For women of child bearing potential Urine or serum.
- Urine test for cannabinoids
- Physical exam
- Baseline Patient Reported Outcomes (ASCQ-Me survey domains for pain impact, emotional impact, social impact, stiffness, and sleep, PROMIS domains for pain impact, neuropathic pain, nociceptive pain, cognitive function, gastrointestinal distress and anxiety. LANSS, PQ-B, C-SSRS)

Data will be collected from five sources: 1) Validated patient reported outcome surveys at baseline, and weeks 4 and weeks 8; 2) Timeline Follow-Back for hospital utilization use at research visits at weeks 4 and 8; 3) medical interview and physical examination at screening, weeks 4 and weeks 8; 4) laboratory markers of inflammation including IL1b, IL4, IL6, IL10, VCAM-1 and TNFα, tryptase, and substance P at baseline, weeks 4 and weeks 8 5) urine toxicology tests at baseline and weeks 4 and weeks 8, 6) safety laboratory tests of renal function, liver function, complete blood count and reticulocytes and pregnancy at screening and at weeks 4 and weeks 8;

In-person screening research interview, screening medical interview and physical examination data will be recorded on paper data collection instruments that identify participants only by unique study ID number. Patient reported outcome surveys will be performed on an I-Pad and entered automatically into REDCap. Data will be entered into a password-protected, encrypted web-based REDCap database, and paper documents will be filed in a locked cabinet.

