Urine toxicology tests will be performed at baseline and blood tests for cannabinoids at weeks 4 and weeks 8. Specimens will be labeled with the name of the research study, the date and time of collection, and the specimen number; no names or other identifying information will be used. The specimen number will be generated using the subject’s study ID number, the letters UT (to denote urine toxicology test), and the visit number. The laboratory will run toxicology tests for THC, methadone, opiates, cocaine, barbiturates, PCP, amphetamines, alcohol, and benzodiazepines on each specimen. The laboratory results will be available to [name] and the study assistant via the HIPAA compliant, encrypted, password protected clinical information system. They will not be reviewed until after the subject has completed the study to protect the masking.

We will conduct a blood test at screening and at weeks 4 and 8.  Laboratory markers of inflammation including IL1b, IL4, IL6, IL10, VCAM-1 and TNFα, tryptase, and substance P and safety laboratory tests of renal function, liver function, complete blood count and reticulocytes and pregnancy at screening and at weeks 4 and 8.

Assessments at weeks 2 and 6 are safety assessments only which consist of self reported adverse events, the PQ-B and the CSSR. These visits may be completed as in person or telemedicine visits.

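### The secondary-analysis exclusion for outside cannabinoid use reads urine for non-THC cannabinoids, contradicting the protocol's blood-only plan, and has no clause for THC found on placebo

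*Protocol*

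**What the plan says.** Section 9.3 makes ITT the primary analysis of every endpoint. It then defines a secondary analysis that drops early leavers, participants with low pill counts and "any patients whose urine samples show presence of cannabinoid metabolites other than THC". Section 9.4.1 repeats this rule in the same terms. Neither section distinguishes the arms.

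The section headed Study Intervention Compliance (6.4 in the table of contents) says how these measures feed the non-ITT analysis. Pill count and blood serve to judge intake of study drug. For outside use the specimen is restricted: "adherence to avoidance of other cannabinoid containing substances (blood only". The assay is broad: "Blood cannabinoids test will be done for multiple cannabinoids including THC, cannabidiol (CBD), and others". It is interpreted by pattern. One state is "recent dronabinol alone in which only THC will be present"; another is "recent cannabis use, without or with dronabinol, in which multiple cannabinoids will be present"; the third is no cannabinoids at all. Blood for this is taken at weeks 4 and 8.

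Section 8.1 gives the toxicology panel, in a paragraph whose specimen code denotes urine toxicology: "The laboratory will run toxicology tests for THC, methadone, opiates, cocaine, barbiturates, PCP, amphetamines, alcohol, and benzodiazepines on each specimen". On timing, that paragraph says "Urine toxicology tests will be performed at baseline and blood tests for cannabinoids at weeks 4 and weeks 8", while the list of data sources earlier in 8.1 has "urine toxicology tests at baseline and weeks 4 and weeks 8".

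**The concern.** The secondary analysis is meant to show the treatment contrast among participants who took study drug and avoided other cannabinoids. Its exclusion rule names a specimen that the compliance section does not use for this purpose, and an analyte class that the listed panel does not report. An analysis plan written from this protocol would inherit two incompatible rules for one population.

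The wording also treats THC as uninformative in both arms. That is reasonable on dronabinol, where THC is the study drug. On placebo, THC should not be there, yet a THC-only result never triggers exclusion. At stake is whether the secondary population is what it is described to be. The trial's primary conclusion is not in question.

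**Working it through.** No figure in the plan is disputed, so the check sets the sections side by side and applies the rule to each possible case.

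**Inputs**
- Rule: exclude if a cannabinoid other than THC is found, regardless of arm (9.3, 9.4.1).
- Urine panel: THC is the only cannabinoid listed (8.1).
- Blood assay: THC, CBD and others. Dronabinol alone gives THC only; cannabis gives several cannabinoids (compliance section).
- Reading adopted: a positive THC entry on the urine panel counts as THC, so metabolites of THC itself do not count as other cannabinoids.

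**Cases: two arms by three kinds of outside exposure**

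| Arm | Outside exposure | Urine panel shows | Rule on urine panel | Blood assay shows | Same rule on blood | Blood plus placebo clause |
|---|---|---|---|---|---|---|
| Dronabinol | none | THC | kept | THC | kept | kept |
| Dronabinol | cannabis | THC | kept | THC and others | excluded | excluded |
| Dronabinol | THC-only product | THC | kept | THC | kept | kept |
| Placebo | none | nothing | kept | nothing | kept | kept |
| Placebo | cannabis | THC | kept | THC and others | excluded | excluded |
| Placebo | THC-only product | THC | kept | THC | kept | excluded |

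Four of the six cases involve outside exposure. The rule removes 0 of 4 on the urine panel and 2 of 4 on the blood assay. With a clause that any cannabinoid counts on placebo, the blood-based rule removes 3 of 4. The remaining case, a THC-only product taken on top of dronabinol, looks the same as study drug on either test. No case without outside exposure is wrongly excluded in any column.

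**Timing**
- Schedule of Activities (1.3): urine toxicology at baseline, week 4 and week 8; no row for blood cannabinoids.
- 8.1, list of data sources: urine at the same three times.
- 8.1, specimen paragraph: urine at baseline, blood at weeks 4 and 8.
- 6.3: refers to urine toxicology after randomisation, with results withheld from the study team.
- Compliance section: blood at weeks 4 and 8.

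The sections disagree on whether urine is tested after randomisation. The result in the table does not depend on this: even with urine at weeks 4 and 8, the listed panel contains no cannabinoid other than THC. The Schedule of Activities omits the one assay that could support the rule.

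**The case against.** The strongest reply is that this is a slip of specimen wording. The right assay is already planned, and if the team uses it, ordinary cannabis use is caught in both arms. Section 2.2 reports the pilot's urine results for THC and other cannabinoid metabolites, so the phrase may have been carried over. Contamination may also be rare: daily users are excluded, a negative urine test is required before randomisation, and none of the 6 pilot participants had cannabinoids in urine during washout or the placebo phase. Finally, anyone wrongly kept here is also in the ITT set, so the flaw adds no bias beyond ITT; it fails to remove some.

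Most of this stands and limits the point. It does not remove it: the pilot's testing is not the panel stated for this trial, the rule is fixed twice in terms that conflict with the compliance section, and moving to blood still leaves the placebo gap.

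Some stronger readings are not supported:
- A reader might infer from one sentence in 8.1 that no urine exists after randomisation. Sections 1.3 and 6.3 and the list in 8.1 say otherwise.
- A reader might infer that outside cannabis use goes undetected in this trial. That is true of the urine wording, not of the blood plan.
- A reader might take the expected 50% of past-year users, suppose that 10% to 20% of placebo participants are exposed with full benefit, and conclude that a 5-point contrast shrinks to 5 × 0.90 = 4.5 or 5 × 0.80 = 4.0. Those shares are assumed. Past-year use includes CBD products and does not estimate THC-only exposure on placebo, for which the protocol gives no rate.
- A reader might say that THC on placebo proves outside use. A dispensing or assay error could produce the same result.

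**Conclusion.** The point holds as a contradiction and a gap in the definition of a secondary population. As written, and on the panel listed in 8.1, the rule excludes nobody for outside cannabis use. On the blood assay it works for ordinary cannabis use but keeps placebo participants with THC alone. This rests on reading the 8.1 panel as the complete urine panel, and on THC's own metabolites not counting as other cannabinoids. The protocol does not settle the second question. If they did count, adherent dronabinol participants could be excluded, which is a further reason to name the analytes.

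No size of dilution should be claimed. The ITT primary analysis and the sample size in 9.2 are untouched. The change should be made before unblinding, but the trial's main result does not depend on it.

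**What to change.** In 9.3 and 9.4.1, replace urine with the week-4 and week-8 blood cannabinoid assay of the compliance section and name the analytes that count. Exclude participants in either arm with any non-THC cannabinoid, and placebo participants with any cannabinoid including THC. Fix the rule beforehand and apply it after unblinding.

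Add the blood cannabinoid assay to the Schedule of Activities, and reconcile the urine toxicology timing across 1.3, 6.3 and the two statements in 8.1.

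The cost is wording and one schedule row, since the assay is planned and blood is already drawn at weeks 4 and 8. The statistical price is asymmetry: THC-only outside use can be detected on placebo but not on dronabinol, so the clause selects after randomisation in one arm only. State this limit and keep the analysis secondary to ITT. Do not turn THC-negative blood on dronabinol into an exclusion on the present text; that would need a detection window, which the protocol does not give.
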